## Abstract

**Background:**

Young men in South Africa face concurrent epidemics of HIV, drug and alcohol abuse, and unemployment. Standard HIV prevention programs, located in healthcare settings and/or using counseling models, fail to engage men. Soccer and vocational training are examined as contexts to deliver male-specific, HIV prevention programs.

**Methods:**

Young men (*n* = 1200) are randomly assigned by neighborhood to one of three conditions: 1) soccer league (*n* = 400; eight neighborhoods); 2) soccer league plus vocational training (*n* = 400; eight neighborhoods); or 3) a control condition (*n* = 400; eight neighborhoods). Soccer practices and games occur three times per week and vocational training is delivered by Silulo Ulutho Technologies and Zenzele Training and Development. At baseline, 6 months, 12 months, and 24 months, the relative efficacy of these strategies to increase the number of significant outcomes (NSO) among 15 outcomes which occur (1) or not (0) are summed and compared using binomial logistic regressions. The summary primary outcome reflects recent HIV testing, substance abuse, employment, sexual risk, violence, arrests, and mental health status.

**Discussion:**

The failure of men to utilize HIV prevention programs highlights the need for gender-specific intervention strategies. However, men in groups can provoke and encourage greater risk-taking among themselves. The current protocol evaluates a male-specific strategy to influence men’s risk for HIV, as well as to improve their ability to contribute to family income and daily routines. Both interventions are expected to significantly benefit men compared with the control condition.

**Trial registration:**

ClinicalTrials.gov registration, NCT02358226. Registered 24 November 2014.

**Electronic supplementary material:**

The online version of this article (10.1186/s13063-018-2804-3) contains supplementary material, which is available to authorized users.

## Background

The DREAMS Initiative was launched by global donors to reduce adolescent and young women’s risks for acquiring HIV [1]. Concurrently, Option B+ is being broadly implemented to eliminate perinatal HIV transmission and increase the length and quality of the lives of women living with HIV in sub-Saharan Africa [2]. While women almost always acquire HIV from their male partners, there are few such initiatives for men nor have men been successfully engaged in HIV prevention or care [3]. This study examines a gender-specific HIV prevention strategy for South African men.

HIV incidence among young, black men in South Africa has remained stable at 3% per year [4], resulting in 2.4 million South African men infected with HIV [5, 6]. New infections occur at an older age among men compared with women [6] and are associated with a cluster of risky behaviors. For example, poly substance use is endemic in South Africa; about 30% of young men report visiting bars more than 10 times per month, 30% have symptoms of alcohol dependency, 50% have recently used marijuana, 32% use methamphetamine, and 20% use mandrax (methaqualone/quaalude, a sedative/hypnotic) [7–11]. Substance use often leads to township violence [12] and is linked to 60% of automobile accidents, 75% of homicides, 67% of domestic violence, and 30% of hospital admissions [13]. Alcohol use alone costs South Africa about 9 billion South African Rand (ZAR) annually [14]. Furthermore, about half of township men have been arrested or are in jail, 22% have been in prison, and 20% report being gang members [11]. More than a third of young men have had recent concurrent sexual partnerships, fail to use condoms [15–18], and experience repeated sexually transmitted infections (STIs) [19, 20]. Almost 30% of young men report that at some point they have forced a woman to have sex [11]. Thus, there are substantial data showing that South African men are in need of efficacious interventions to reduce their risk for HIV, and their HIV risk appears related to a cluster of risky acts.

While men experience many risks, HIV prevention resources are primarily anchored in healthcare settings—a setting underutilized by men [21, 22]. In particular, most women find out about their HIV infection in antenatal care, a setting which men are typically excluded from visiting [22]. Seropositive men seek care at much later stages of disease than women [23].

One explanation for men’s underutilization of healthcare is the incompatibility of existing intervention models with young men’s identities, roles, and preferred styles of acting [11, 24, 25]. Existing evidence-based interventions (EBI) for HIV are based on counseling models of “tend and befriend”, which are common female strategies for coping with stress [26]. In contrast, men more often utilize a “fight or flight” strategy for coping with stress [26]. Traditionally, men’s engagement in EBI for HIV has been lower than that of women [27].

Young South African men need new pathways for prosocial roles and behaviors. Concurrently, interventions need to be attractive and consistent with men’s styles. We have designed a behavioral intervention around soccer to “pull” or engage men in the intervention, rather than having to “push” public health strategies into their lives. For men, sports activities are highly attractive activities and promote a social and personal identity [28]. South Africans associate soccer with a strong sense of national identity [29] and sports elicit strong feelings of masculine identity [30]. Soccer potentially creates a replacement for the strong masculine roles in tribal society that were destroyed with rapid migration to peri-urban settlements in the Western Cape of South Africa. In the context of having fun or planning for the future, young men acquire healthy habits of daily living and reinforce positive community norms. In our pilot study, soccer was a highly desirable activity; 95% of men enrolled in the pilot and 80% were successfully engaged on a sustained basis, participating in roughly three practices and a game weekly over 6 months [11]. Even if they were not good players, the young men valued being part of the team. In qualitative interviews, families felt uniformly positive about soccer. It occupied young men, gave them respect in the community, and games were an opportunity for the community to attend and value the young men.

In addition, there is evidence that sports and physical activity are associated with reduced rates of substance abuse and HIV risk [31–33], and have been recognized as a rewarding public health strategy [34]. Similarly, sports programs promote healthy daily habits. Requiring young men in the intervention to consistently arrive on-time, attend practices, and to be drug-free mirrors the requirements for employment. The soccer intervention may establish these habits, create prosocial networks between men, and offer men opportunities to demonstrate their reliability. Their soccer networks may also provide new relationships and opportunities for linking to employment.

Linking to employment is critical. Unemployment is normative in South Africa’s townships, affecting 7 million persons annually [6, 35]. In Cape Town, 66% of young people are unemployed and many face lifetime unemployment [36]. Men have also been largely excluded from economic development programs [37, 38], even though these interventions have similar outcomes across gender [39, 40]. There are typically no community centers that engage young people, and the majority of young men stop school at 10th grade [41].

In 2000, the South African government established the Services Sector Education and Training Authority (SSETA), a job training program operated by the Department of Labor [42]. Although there is an annual budget of more than ZAR 3 billion, fewer than 0.9% of youth receiving the vocational training from SSETA are provided with any type of on-the-job training and 60% are unemployed at the completion of the program [43]. When young people are finished with job training, there is no network to find jobs and young people do not have the tools to initiate their own businesses [44]. The government offers ZAR 350 to provide apprenticeships; however, this requires about 10 h of paperwork per month by both the employer and employee to access the monthly stipend and additional tax breaks [45]. Given these challenges, apprenticeships are underutilized and SSETA funds are consistently underspent annually [45]. Interpersonal support is missing from the job training programs of the South African government; we plan to provide this through a combination of two programs—the Silulo Ulutho Technologies and Zenzele Training and Development—in the proposed intervention. Silulo Ulutho Technologies, established in 2004, is an award-winning infrastructure technology (IT) company that offers specialized training programs through their Training Academy. For the proposed project, Silulo provides accredited public computer courses. Zenzele Training and Development, based in Khayelitsha, provides training in vocational and business skills, as well as mentorship. Zenzele, which means “do it yourself” in Xhosa, was established in the late 1990s. For the proposed project, Zenzele offers accredited courses on woodwork and welding. Between the two programs, participants have opportunities to develop both the interpersonal and vocational skills required for gainful employment.

In a pilot evaluation of this intervention, we found that 30% of young men secured jobs (despite none having employment at baseline) [11]. We trained men for five different jobs: painting, electrical work, construction, mobile phone repair, and plumbing. The training was useful to some young men; however, assisting young men in job preparation or placing them in a position needs to be highly personalized. We provided clothes for job interviews, business cards, and helped young men find potential job opportunities. We are building on these interpersonal strategies in the proposed randomized controlled trial (RCT) with both the Silulo Ulutho Technologies and Zenzele Training and Development programs.

This paper summarizes the protocol of the RCT being implemented in the townships of Cape Town, South Africa, to evaluate the efficacy of this strategy. Twenty-four neighborhoods are randomized to one of three conditions: 1) soccer training; 2) soccer and vocational training; or 3) a control condition. The primary hypothesis is that there will be an overall significant improvement in the number of significant outcomes (NSO) found among 15 correlated outcomes, which will be assessed over 24 months comparing the soccer, soccer plus vocational training, and the control conditions. Figure 1 outlines the underlying theoretical model and Fig. 2 shows the schedule of enrollment, interventions, and assessments (SPIRIT figure).

**Fig. 1 Fig1:**
[figure not shown]
Relationships among contextual/background factors, mediating/moderating influences, intermediate outcomes, and primary and secondary outcomes. ARV antiretroviral, AUDIT Alcohol Use Disorders Identification Test, RDT rapid diagnostic tests, ZAR South African Rand

**Fig. 2 Fig2:**
[figure not shown]
Schedule of enrolment, interventions, and assessments

## Methods/design

### Ethical approvals and management structure

The Institutional Review Boards (IRB) of the University of California, Los Angeles (UCLA; IRB no.14–001587) and Stellenbosch University (N14/08/116) approved the current study protocol (Version 3.0, 1 June 2018). The IRBs approve any changes to the study protocol, and the Clinical Trials registration is updated in the event of protocol modifications. The study protocol follows the Standard Protocol Items: Recommendations for Interventional Trials (SPIRIT) and the populated checklist is provided as an Appendix (see Additional file 1). Authorship is based on standards outlined by the American Psychological Association [46].

### Data monitoring

We formed an independent Data Safety Monitoring Board, comprised of four consultants with substantial research experience in South Africa and the United States. The DSMB meets twice annually and reviews interim analyses after each round of follow-up data collection at 6, 12, and 24 months. Stopping the trial will occur only if there appears to be iatrogenic effects associated with men meeting in groups and exacerbating each other’s risk acts. In particular, we monitor criminal acts, sexual risk, and increased substance use that could be associated with the intervention at the 6- and 12-month interim analyses.

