### Assessments

At the local storefront assessment center, trained interviewers obtain written voluntary informed consent and then administer a 1-h assessment, recording responses on mobile phones using a program designed by Mobenzi Technologies. Participants receive about ZAR 150 for their time to complete the interview (incentives are adjusted over time for inflation). Assessment data are coded with personal identification numbers (PIDs) and do not include any personally identifiable information. De-identified assessment data are available through a password-protected, cloud-based database and accessed by UCLA and Stellenbosch University for quality control and later analyses. Assessments are conducted at the baseline recruitment and at 6, 12, and 24 months later. Interviewers report all adverse events to their supervisors in real time and identify these as study-related (or not). Serious adverse events (death, criminal acts) are reported to all Investigators, Institutional Review Boards, and funding agencies within 48 h.

At the time of enrollment, interviewers collect detailed locator information from participants, including the names and addresses of friends and family members and favorite hangout spots, locally and in the Eastern Cape, where the ancestral homes of many Cape Town residents are located. The Assessment Team, led by Stellenbosch University, is experienced in using this information to retain participants, consistently maintaining participant retention rates at or above 85% [48].

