### Intervention

All young men in a neighborhood are assigned to the same condition. Participants will be removed from the study if they directly threaten or are physically violent toward any study staff or other participants, or if they are seriously disruptive or verbally abusive to peers or staff during soccer training, a soccer game, or assessment at least three times in a 2-week period. On a weekly basis, participants in the intervention conditions are tested for substance use. Any participant with a positive drug or alcohol screen is barred from attending the intervention that day.

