#### Condition 2: soccer league (SL)

All young men in eight neighborhoods (*n* = 400) receive soccer training for 1 year. After all of the baseline assessments are completed in a specific neighborhood, soccer coaches visit each participant individually to describe the intervention in detail, invite them to the soccer league, and answer any questions. The league includes at least two and usually three teams per neighborhood (14 men minimum per team needed, anticipating some absenteeism), resulting in approximately up to 24 teams in this condition. Each week, there are 2 days of practice and 1 day for a game with another team. Teams are led by coaches who are recruited from the broader township (versus target neighborhoods) to safeguard players’ confidentiality (coming from the same neighborhood is likely to inhibit men’s disclosures about problem issues, fearing the coach may tell others). Coaches cannot be regulars at the local shebeens or known drug addicts, and must have held a job at some time previously, have experience playing soccer, and demonstrate good social skills. In this way, coaches are positive peer deviants (i.e., role models) for participants [53, 54]. About 30% of persons applying to be coaches are hired, based on initial interviews and observations completed during the coach training.

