#### Condition 3: soccer league and vocational training (SL-V)

For the first 6 months of intervention delivery, all procedures described above for the SL condition are replicated for all young men in eight neighborhoods (*n* = 400 men). The selection, training, and monitoring system for coaches and participants is the same in both conditions for the first 6 months, with soccer offered 2 days per week and a game on Saturdays.

After 6 months, all young men are offered vocational training through either Silulo Ulutho Technologies or Zenzele Training and Development programs. In these programs, participants have access to accredited training programs in public computer courses, woodwork, and welding. Both programs are located in Khayelitsha, which is close to participants’ homes, thus avoiding transport-related barriers. Additionally, the training programs occur in a mentor-mentee context so that participants can develop the interpersonal skills required for employment.

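### The stopping sentence admits one route to harm only, so as written it excludes stopping the trial for other serious study-related harm (minor wording defect)

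*Protocol article*

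**What the plan says.** The Data monitoring section of the protocol article sets up an independent Data Safety Monitoring Board (DSMB). The board meets twice a year and reviews interim analyses after the 6-, 12- and 24-month follow-up rounds. The section then gives the rule for ending the trial: "Stopping the trial will occur only if there appears to be iatrogenic effects associated with men meeting in groups and exacerbating each other’s risk acts". The next sentence says what is watched at the 6- and 12-month looks: "In particular, we monitor criminal acts, sexual risk, and increased substance use that could be associated with the intervention".

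Adverse events are handled in the Assessments section. Interviewers pass every adverse event to a supervisor at once and label it as related to the study or not. For the serious ones: "Serious adverse events (death, criminal acts) are reported to all Investigators, Institutional Review Boards, and funding agencies within 48 h".

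The Intervention section has rules for individual conduct, among them: "Participants will be removed from the study if they directly threaten or are physically violent toward any study staff or other participants". It also bars a man with a positive drug or alcohol screen from that day's session.

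The section on ethical approvals gives the IRBs approval of any change to the protocol.

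**The concern.** A safety stopping rule should be at least as wide as the harms the trial is set up to recognise. Here the adverse event procedure is general: any event can be classed as caused by the study, and death is named as serious. The stopping sentence is narrow: it allows one causal route and, through the words *only if*, shuts out the rest.

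Taken at its word, a study-related death or serious injury that did not come from men worsening each other's risk behaviour would be reported but would not be a stated ground for stopping. What is at stake is the clarity of a participant-safety rule. No estimate, test or sample size depends on it.

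**Working it through.** There is no figure to reproduce and no formula applies. The check is whether the exclusive reading survives a comparison with the rest of the article.

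1. **Form of the rule.** The sentence makes one condition necessary for stopping. It therefore excludes stopping for efficacy, for futility, and for any harm that does not arise through the named mechanism. The first two exclusions look deliberate. The third is the defect.

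2. **Does the following sentence widen it?** No. Criminal acts, sexual risk and substance use are all risk behaviours, so they illustrate the same mechanism. The list is introduced as particular examples and so leaves *monitoring* open to other items. It does not loosen the condition for *stopping*.

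3. **Does another section supply a second ground?** Four places were checked:
   - Assessments governs the capture, classification and reporting of adverse events and does not link them to stopping.
   - Intervention removes or bars individual men and says nothing about ending the trial.
   - Data management says that the statistical team supplies ongoing analyses to the DSMB and gives no stopping ground.
   - Ethical approvals and management structure covers IRB approval of protocol changes and gives no stopping ground.

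   None states a second trial-level ground.

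4. **Is there any other route to harm?** The activities make one conceivable. In the soccer arm, "Each week, there are 2 days of practice and 1 day for a game with another team", for 1 year. In the arm that adds vocational training: "In these programs, participants have access to accredited training programs in public computer courses, woodwork, and welding". Serious injury at play or in a workshop would not be peer exacerbation of risk acts. These examples are supplied by this review. The article does not name injury as a risk and gives no rate, so the size of the risk cannot be stated.

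5. **What is already covered.** A death or other serious event that does follow from men worsening each other's risk behaviour falls within the stated ground. The gap is confined to serious study-related harm by other routes.

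**The case against.** The strongest reply is context. The sentence stands between a statement that the DSMB reviews interim analyses and a statement of what is monitored at those analyses. Read there, it says when interim outcome data would end the trial: for peer contagion, and not for benefit or futility. That fits the worry about men in groups in the abstract and the Discussion. Event-driven safety runs through a separate channel, with immediate reporting of adverse events and 48-hour reporting of serious ones to the investigators, IRBs and funders. The full protocol (Version 3.0) and any DSMB charter are not shown and may give wider grounds.

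Most of this stands, and it is why the weight is low. It does not remove the point. The sentence does not say that it is limited to efficacy and futility, and its literal effect goes further. This is not detail left to another document but an exclusive statement in the published text; a charter that allowed stopping for other harm would contradict it.

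Three stronger readings are tempting, and the article supports none of them.

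- A reader might infer that the DSMB or the IRBs are barred from halting the trial for other harm. Nothing in the article limits what either body may recommend or order.
- A reader might infer that deaths go unmonitored because death is not on the interim list. That list is expressly not exhaustive, and deaths are reported individually within 48 h.
- A reader might infer that the DSMB is not told of serious events because it is not named among the 48-hour recipients. Its absence from that list does not show that it is uninformed.

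**Conclusion.** The point holds as a minor defect of safety wording. As published, the only stated ground for stopping is peer exacerbation of risk behaviour, worded so as to exclude other serious study-related harm that the trial's own adverse event procedure is built to recognise.

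The conclusion rests on the literal wording and on the article being the only document at hand. It assumes nothing about how often such harm would occur. If the sponsor's intent was only to exclude stopping for efficacy or futility, which is likely, the sentence says more than was meant and the correction is editorial. IRB oversight remains a safeguard in either case.

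**What to change.** Replace the stopping sentence in the Data monitoring section with:

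> There is no early stopping for efficacy or futility; the trial may be paused or stopped for serious study-related harm, including iatrogenic effects that arise when participants in groups reinforce one another's risk behaviour.

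This keeps the probable intent, retains the peer-group concern as a named instance, and removes the unintended exclusion. It adds no efficacy or futility look.

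The cost is one sentence of protocol wording, passed through the IRB approval already required for protocol changes, with the trial registration updated as that section also provides. No new data, visits, analyses or participants are needed. Recruitment was still under way when the article was submitted, so at that stage the change could have been made during the trial.
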